## Abstract

**Background:**

There is no clear evidence that early decompression following spinal cord injury (SCI) improves neurologic outcome. Such information must be obtained from randomized controlled trials (RCTs). To date no large scale RCT has been performed evaluating the timing of surgical decompression in the setting of thoracolumbar spinal cord injury. A concern for many is the ethical dilemma that a delay in surgery may adversely effect neurologic recovery although this has never been conclusively proven. The purpose of this study is to compare the efficacy of early (before 24 hours) verse late (24–72 hours) surgical decompression in terms of neurological improvement in the setting of traumatic thoracolumbar spinal cord injury in a randomized format by independent, trained and blinded examiners.

**Methods:**

In this prospective, randomized clinical trial, 328 selected spinal cord injury patients with traumatic thoracolumbar spinal cord injury are to be randomly assigned to: 1) early surgery (before 24 hours); or 2) late surgery (24–72 hours). A rapid response team and set up is prepared to assist the early treatment for the early decompressive group. Supportive care, i.e. pressure support, immobilization, will be provided on admission to the late decompression group. Patients will be followed for at least 12 months posttrauma.

**Discussion:**

This study will hopefully assist in contributing to the question of the efficacy of the timing of surgery in traumatic thoracolumbar SCI.

**Trial Registration:**

RCT registration number: ISRCTN61263382

## Background

The role and timing of surgical decompression after an acute spinal cord injury (SCI) remains one of the most controversial topics pertaining to spinal surgery [1]. Despite an enormous amount of interest and research in SCI, the prognosis for neurologic recovery in patients with a severe SCI remains poor. Acute SCI remains an important cause of morbidity and mortality. Furthermore, the majority of patients with SCI are young, making the economic and societal impact immense [2].

Acute SCI involves both primary and secondary mechanisms of injury. The primary mechanism, usually caused by rapid spinal cord compression caused by bone displacement from a fracture-dislocation or burst fracture, is irreversible. It also initiates a cascade of secondary injury mechanisms, including ischemia, electrolyte derangements, and lipid peroxidation. Secondary injury is preventable and may be reversible [3].

The increased understanding of the pathophysiology of acute SCI has led to clinically relevant neuroprotective therapies to attenuate the effects of the secondary injury. The National Acute Spinal Cord Injury Studies (NASCIS II and NASCIS III) have shown a modest beneficial effect of high-dose methylprednisolone if given within 8 hours of injury in patients with SCI [4,5].

There is experimental evidence that persistent compression of the spinal cord is a potentially reversible form of secondary injury [6-10]. Dimar et al (1999) and Carlson et al (2003), Rahimi-Movaghar et al (2008) demonstrated in animal models that early decompression showed significantly better functional recovery and significantly smaller lesion volumes than delayed surgical intervention.

There are several prospective studies of surgical decompression in acute SCI [11-20]. In a non-randomized study, Papadopoulos et al (2002) evaluated 91 patients with acute cervical SCI to assess the feasibility and outcome of an immediate decompression treatment protocol. All patients, except 1, were admitted within 9 hours of their injury. The investigators reported that 39/66 patients in the protocol group had improvement following early surgery, including some presenting with a complete SCI, compared to 6/25 in the control group. They suggested that patients who had decompression with closed reduction alone (mean time to decompression 6.0 hours) had better neurologic outcomes than those requiring surgical decompression (mean time to decompression 12.6 hours) [13]. La Rosa et al (2004) performed a systematic review of all available studies published between 1966 and 2000. They concluded that early (<24 hours) surgical decompression in patients with incomplete injuries resulted in better neurologic outcomes than patients treated with either delayed decompression (>24 hours) or nonoperative treatment [21]. In contrast, several prospective studies have failed to document a beneficial effect of surgical decompression [11,12,19,20]. However, no study to date has truly examined in a systematic way a large cohort of randomized surgical patients who underwent decompression earlier than 24 hours. For example, although the study by Vaccaro et al (1997) was a prospective, randomized trial, 20 of the 62 patients were lost to follow-up, and "early" surgery was defined as being within 72 hours after SCI [12].

In contrast to the aforementioned studies of early decompression, Larson et al (1976) advocated operating a week or more after SCI to allow medical and neurologic stabilization of the injured patient [22]. This remains the practice in many institutions, particularly in light of early reports suggesting an increased rate of medical complications with early surgery (<5 days after SCI) [23]. Interestingly, a number of investigators have documented recovery of neurologic function after delayed decompression of the spinal cord (months to years) after the injury [24,25].

In the cases of incomplete thoracolumbar SCI, there are some criticisms for no surgery, because first, there is some evidence for effectiveness of decompression, second, instability could be harmful and increase neurologic deficit [26].

This RCT will try to evaluate the efficacy of surgical intervention in the setting of thoracolumbar spinal cord injury as has been done in previous retrospective studies [27,28]. Thus, we chose patients with acute spinal cord injury from T1 to L1. The clinical benefits of early or late surgery in improving neurologic recovery remains controversial because of the absence of well-designed and well-executed prospective, randomized controlled multi-centered trial.

In this study proposal, SCI patients with documented spinal cord compression will be assigned to either an early (<24 hrs) or later (24–72 hrs) decompression group (control group). The reason for choosing 24 hours as the cutoff for early decompression is that while NASCIS 2 & 3 trials [4,5] demonstrated benefit to patients treated within 8 hrs of their SCI, a multi-centered feasibility study conducted at SCI centers has demonstrated difficulty in instituting clinical treatment within an 8-hour time frame from the moment of injury [14]. This is a reflection of the time needed to transport a patient from the accident scene to a nearby hospital, then a Level I trauma center, and then to a MRI scanner to confirm the presence and location of spinal cord compression. Thus the 24-hour cutoff for early decompression was chosen as this represents an early decompression time frame that could realistically be applied to a clinical population of spinal cord injured patients.

In the last decade, many SCI clinical researchers have noted that RCTs are required in order to define the role of surgery in the management of acute SCI more properly [1,21,27,28], but withholding SCI patients who arrive early in the emergency room from early surgical decompression may not be acceptable by some surgeons.

The objectives of this study are to examine the benefits of neural decompression and its' relationship with neurologic improvement in regards to timing of intervention.

### Purposes

#### Primary purposes

To determine whether early or late surgical decompression is effective in neurological improvement in the setting of traumatic spinal cord injury from T1 to L1.

#### Secondary purposes

-To compare the neurological improvement in summed ASIA motor scores 12 months following a complete SCI in each of the early and late group of decompression

-To compare the neurological improvement in summed ASIA motor scores 12 months following an incomplete SCI in the early and late group following decompression

-To assess fusion success in the early and late group following decompression

-To assess sagittal alignment at the fracture level in the early and late group following decompression

-To compare the duration of acute hospitalization in the early and late group following decompression

-To compare the overall length of acute hospital stay in the early and late following decompression

-To compare the overall length of chronic hospital stay for rehabilitation [22] in each of the early and late decompression

-To assess the incidence of mortality in the early and late group following decompression

- To determine the frequency of complications in the early and late group following decompression

## Methods

### Design of Study

The study is intended to be a randomized clinical trial study.

### Sample size

The proportion of patients demonstrating at least a 5-point improvement in summed motor score in a previous study at our institution evaluating the timing of decompression in a complete SCI was 9% (*p*2) [28]. What we expect to be an intended (or at least acceptable) effect of the early decompression group is 33% of patients demonstrating at least a 5-point improvement in summed motor score (*p*1) [19]. To detect this difference with a sensitivity of 80% and an error probability of 5%, at least 149 patients per randomization group will be required using the following formula:

Considering only comparing the two groups of early and late decompression, our sample size should be at least 298 cases. To account for the possibility of 10% loss to follow-up, our estimated sample size is 328 cases.

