### Randomization

Using blocked sample randomization generates the randomization list. The permuted block method of randomization for a block size of four was used. Complete and incomplete SCI patients each are allocated to the two groups, early (E) and late (L).

Randomization will be stratified by site. Separate blocked sequences will be allocated to each of 4 sites, therefore patients referred to a particular site will be randomized regardless of the treatment sequences of other sites.

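### The 9% control rate behind the sample size comes from complete injuries only, but the primary comparison pools complete and incomplete injuries, so the stated 80% power does not describe it

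*Protocol article*

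**What the plan says.** **Planning rates (Sample size).** The control responder rate, meaning a gain of at least 5 points in summed motor score, comes from institutional work "evaluating the timing of decompression in a complete SCI was 9" per cent. For the other arm: "What we expect to be an intended (or at least acceptable) effect of the early decompression group is 33% of patients". The section continues "with a sensitivity of 80% and an error probability of 5%, at least 149 patients per randomization group will be required", then "our sample size should be at least 298 cases", and finally "To account for the possibility of 10% loss to follow-up, our estimated sample size is 328 cases".

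**Population.** The primary purpose covers traumatic cord injury from T1 to L1 with no limit on severity. Under Exclusion criteria, the only grade on the ASIA Impairment Scale that bars entry is E. The Randomization section says "Complete and incomplete SCI patients each are allocated to the two groups, early (E) and late (L". Complete and incomplete injuries are compared separately only as secondary purposes, for example motor improvement "12 months following an incomplete SCI in the early and late group following decompression".

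**Analysis.** Descriptive and Explorative Statistics names the dichotomous improvement outcome as the main analysis and adds multivariable and logistic regression. The factors named in Control for Potential Confounding Factors are age, sex, mechanism of injury and associated injuries. Completeness of injury is not among them.

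**The concern.** A power statement holds only for the population its rates describe. Here the control rate belongs to one severity stratum, while the primary comparison pools two. Incomplete injuries would be expected to gain 5 motor points more often than complete ones, so the pooled control rate is likely to exceed 9%. The article gives no figure for how far.

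A higher control rate matters in three ways. The binomial variance grows, so a given difference is harder to detect. If the early rate stays at 33%, the difference itself shrinks. If the benefit of early surgery is concentrated in complete injury, pooling dilutes it. The reader cannot tell from the planning paragraph which of these applies, or what difference the trial can detect in the patients it will analyse.

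**Working it through.** **Inputs.** From Sample size: control 9%, early 33%, power 80%, error 5%, 149 per group. The section does not say whether the test is one- or two-sided; two-sided is assumed (z = 1.960 and 0.842). Rates for incomplete injury and the case mix are not in the article and are assumptions below.

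**Formulas.** With d = p1 − p2, p̄ the mean of the two rates, A = √[2p̄(1−p̄)] and B = √[p1(1−p1) + p2(1−p2)]:

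- n per group = (1.960·A + 0.842·B)² / d²
- power = Φ[(d·√n − 1.960·A) / B]

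**The plan's own figure.** For 33% versus 9%: p̄ = 0.21, A = √0.3318 = 0.576, B = √0.3030 = 0.550.

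- n = (1.129 + 0.463)² / 0.0576 = 44.02, so 45 per group.
- With continuity correction it is 53. One-sided it is 35, or 43 with correction. Unpooled variance or the arcsine method gives 42. No variant at 80% power comes near 149.
- At 149 per group, power for 9% versus 33% is Φ[(0.24 × 12.207 − 1.129) / 0.550] = Φ(3.27), about 99.9%.
- With a 9% control rate, 149 per group has 80% power for an early rate of about 20.5%, a difference of 11.5 points.
- The later steps do follow: 149 × 2 = 298, and 298 × 1.10 = 327.8, rounded to 328.

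**Power at 149 per group if the control rate is not 9%**

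*(a) Early rate held at 33%*

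| Control rate | Power | n per group for 80% |
|---|---|---|
| 15% | 96% | 88 |
| 19% | 79% | 153 |
| 20% | 72% | 180 |
| 25% | 33% | 504 |

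For the 20% row: d = 0.13, A = 0.624, B = 0.617, so Φ[(1.587 − 1.223) / 0.617] = Φ(0.589) = 0.72.

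*(b) The 24-point difference kept at control rates of 20% to 50%.* The requirement is 59 to 67 per group, and 149 gives about 99% power.

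*(c) The 24-point gain holds in complete injury only.* Let f be the share incomplete and q their improvement rate under late surgery. The pooled control rate is (1−f) × 9% + f × q and the pooled difference is (1−f) × 24 points.

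- f = 0.5, q = 60%: control 4.5% + 30% = 34.5%, difference 12 points, A = 0.694, B = 0.689. Power = Φ[(1.465 − 1.361) / 0.689] = Φ(0.151) = 0.56.
- For q from 40% to 80%: 54% to 61% at f = 0.5, 85% to 91% at f = 0.3, and 24% to 26% at f = 0.7.

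**Difference that 149 per group detects with 80% power**

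| Control rate | Detectable difference (points) |
|---|---|
| 9% | 11.5 |
| 20% | 14.4 |
| 30% | 15.7 |
| 40% | 16.2 |
| 50% | 16.0 |

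**The case against.** **The trial is not shown to be short of patients.** A reader might infer from the mismatch that the trial is underpowered. The documents do not support that. On its stated rates the plan has more than three times the patients it needs (149 against about 45), and a 24-point difference keeps about 99% power at any control rate from 20% to 50%. The 56% figure requires that timing has no effect at all in incomplete injury. That runs against the systematic review described in the Background, which favours decompression before 24 hours specifically in incomplete injuries. On the same 50% and 60% assumptions, a gain of only 8 points in incomplete patients makes the pooled difference 0.5 × 24 + 0.5 × 8 = 16 points and restores about 80% power. This objection stands: the power loss is conditional.

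**The source of the 33%.** A reader might also infer a contradiction from the citation, because the 33% is referenced to a study in the group of which the Background says "several prospective studies have failed to document a beneficial effect of surgical decompression [11,12,19,20". The inference fails. That sentence concerns decompression in general, not early against late. A study that shows no benefit can still report 33% improving in one of its groups. The Sample size section also presents 33% as an expected or acceptable effect, not as an established one.

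**Completeness may already be handled.** Separate comparisons by severity are secondary purposes, adjustment for important prognostic factors is planned, and an analysis plan that is not shown may name completeness. This stands in part. However, the article does name its prognostic factors, and completeness is not among them, although the Randomization section singles it out.

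None of this answers the basic point that the control rate comes from a narrower population than the one analysed.

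**Conclusion.** The mismatch is established from the text: the control rate is for complete injury, the primary comparison is for all eligible injuries, and the stated 80% power therefore does not apply to it. The consequence for power is open. At 149 per group it ranges from about 99% (24 points overall), through 72% and 33% (control 20% and 25%, early rate fixed at 33%), to about 56% (the dilution case with half incomplete). These figures rest on assumed rates and case mix, a two-sided 5% test without continuity correction, and 149 evaluable patients in each group.

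A separate error in the same paragraph is also established: 149 does not follow from the stated inputs, which give about 45. The surplus is what gives the trial room for a higher control rate, so correcting the arithmetic alone, by cutting the sample towards 45, would make the mismatch more damaging.

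The planning paragraph should be corrected. The material does not justify calling the trial underpowered.

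**What to change.** 1. **Sample size.** State the control rate as a mixture of 9% for complete injury and a separate rate for incomplete injury at the expected case mix, and label the incomplete rate and the mix as assumptions.
2. **Sample size.** Replace the 9% versus 33% contrast with the difference that 149 per group detects with 80% power: about 14 to 16 points at control rates of 20% to 50%. State that the test is two-sided. This also removes the figure that does not follow from its inputs.
3. **Control for Potential Confounding Factors.** Add completeness of injury (complete or incomplete) to the listed factors, and stratify the primary responder analysis by it or adjust for it.

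The cost is rewording and one covariate, on a characteristic already used to describe allocation. No extra patients are needed. The detectable difference then stated is smaller than the 24 points now given, so the plan's claim does not become less favourable.

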### Descriptive and Explorative Statistics

Continuous variables including improvement of summed ASIA motor scores, summed ASIA sensory scores (light touch and pin prick) and the FIM scale will be managed with descriptive statistics (mean, SD, minimum, median, and maximum) and will be compared between treatment groups using the T-test.

Noncontinuous data including the occurrence and frequency of medical complications will be analyzed by the X^2 ^technique and organized in tables to include sample size, absolute and relative frequency.

The sample size was conducted on the percent of patients demonstrating an "improvement" in percent summed motor score. It is a dichotomous variable. This is our main method of analysis, but we also record ASIA motor score as a continuous variable to improve the power of our analysis.

In addition to univariable statistics, data will be analyzed by multivariable regression analysis to allow for statistical adjustment for important prognostic (confounding) factors.

Logistic regression is used to estimate the odds ratios and 95% confidence intervals. To perform data analysis, the SPSS-15 software applications are used. A P-value of less than 0.05 is considered statistically significant.

Factors suspected to be unbalanced between the groups would be accounted for by analysis of covariance.

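### The 149 patients per group does not follow from 9% v 33%, 80% power and 5% error, which need about 42 to 53 per group

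*Protocol article*

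**What the plan says.** The protocol article's Sample size section prints every input and the result.

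- **Late-surgery rate:** 9%, from a previous study at the same institution ("evaluating the timing of decompression in a complete SCI was 9" per cent).
- **Early-surgery rate:** the hoped-for effect "is 33% of patients demonstrating at least a 5-point improvement in summed motor score".
- **Result:** "To detect this difference with a sensitivity of 80% and an error probability of 5%, at least 149 patients per randomization group will be required".
- **Totals:** for the two groups together, "our sample size should be at least 298 cases". Adding 10% for loss to follow-up gives 328, the number that the abstract also carries.

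The section on Descriptive and Explorative Statistics confirms that the calculation rests on this improved/not improved endpoint: "It is a dichotomous variable. This is our main method of analysis". It sets the threshold as "A P-value of less than 0.05 is considered statistically significant", without saying whether the test is one- or two-sided.

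The article mentions no further multiplier: no additional arms, no separate powering of complete and incomplete injuries, no multiplicity adjustment and no clustering allowance. A formula is announced, but the equation is not visible in the text available for this review. That gap is not counted against the plan.

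**The concern.** A 24-point difference from a base rate as low as 9% is large and needs few patients, so 149 per group at 80% power looks far too many. If it is wrong, the size, target effect and power of the main analysis cannot all be true, and the article does not show which one is at fault.

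Two things are at stake. The first is interpretation. A null result would be read against 80% power for 24 points, although the trial could detect a considerably smaller difference with that power. The second is the justification for enrolment. If 9% v 33% really is the target, the plan randomizes about three times as many patients as its own assumptions support, in a trial whose Ethics section argues at length that randomizing the timing of surgery is acceptable.

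**Working it through.** **Inputs.** From Sample size: p1 = 0.33, p2 = 0.09, difference 0.24, power 0.80, alpha 0.05. Two-sided testing is my assumption (one-sided is tried below). Allocation is 1:1, implied by 149 per group and 298 in total. So z(0.975) = 1.960, z(0.80) = 0.842, and (1.960 + 0.842)² = 7.849 from unrounded values.

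**1. Attempt to reproduce 149**

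*Unpooled variance:* n = 7.849 × [p1(1−p1) + p2(1−p2)] / (p1−p2)²
= 7.849 × (0.2211 + 0.0819) / 0.0576 = 41.3, so **42**.

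*Pooled variance under the null* (mean rate 0.21): n = [1.960 × √(2 × 0.21 × 0.79) + 0.842 × √0.3030]² / 0.0576
= (1.129 + 0.463)² / 0.0576 = 44.0 (44.015 unrounded), so **45**.

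*Continuity-corrected:* n = (44.015/4) × [1 + √(1 + 4/(44.015 × 0.24))]² = 52.01, so **53**.

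The stated figure is not reproduced. It is 149/53 = 2.8 to 149/42 = 3.5 times the requirement.

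**2. Other routes to 149**

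| Variant on 9% v 33% | n per group |
|---|---|
| One-sided 5%, 80% power | 33 to 43 |
| Arcsine, two-sided | 42 |
| Fisher exact test | about 50 |
| Maximum variance (both rates treated as 50%) | 69 |
| Bonferroni for up to six comparisons | at most 77 |
| 90% power (pooled to corrected) | 59 to 67 |
| 95% power | 72 to 80 |
| 99% power | 101 to 109 |
| 99.9% power | 140 to 148 |

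Only power near 99.9% comes close. Powering the two injury strata separately, which the article does not claim, would double 42–53 to 84–106, still not 149.

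Changing the base rate does not help either. A 24-point difference needs most patients at 38% v 62%: 64.2 (unpooled), 66.9 (pooled) or 75.04 (corrected), so 65 to 76 per group.

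**3. Power at 149 per group**

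For 9% v 33%, normal approximation: z = (0.24 × √149 − 1.960 × 0.5760) / 0.5505 = (2.930 − 1.129) / 0.5505 = 3.27, which is 99.95%. Exact binomial power of the uncorrected chi-square test is 99.96% at 149 per group and 80.6% at 42. In the least favourable case, 38% v 62%, power at 149 is still about 98.8%.

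**4. What 149 per group does correspond to at 80% power**

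| Rate held fixed | Other rate: unpooled / pooled / corrected | Difference |
|---|---|---|
| 9% late | 20.3% / 20.5% / 21.2% | 11 to 12 points |
| 33% early | 19.0% / 18.8% / 18.2% | 14 to 15 points |

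**5. Later steps**

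2 × 149 = 298, and 298 × 1.10 = 327.8, so 328. These follow from 149 as printed, so the inconsistency lies in the 149 itself. The 10% is added afterwards and cannot explain it. With the stated inputs the total before loss would be 2 × 42 = 84 to 2 × 53 = 106.

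**The case against.** The arithmetic is hard to dispute. The best case on the other side concerns its weight and the remedy.

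- **Direction.** For the stated effect the trial has more power than it claims. Type I error and the effect estimate are untouched, and a reader of a null result would be too cautious rather than misled into a false conclusion. This stands. The fault lies in the justification of the size and not in the trial's ability to detect 9% v 33%.
- **Missing formula.** The equation may have shown which input was misprinted. This stands in part. It means that the wrong figure cannot be identified from the text, and a misprinted rate is as possible as a misapplied formula. It does not rescue 149, because inputs and answer are both printed and no standard two-proportion formula connects them.
- **Size of the detectable effect.** About half of 24 points holds with 9% as the anchor. It is nearer 60% when 33% is held fixed. If, as an assumption, the late-group rate were 20% to 40%, the difference detectable with 80% power would be about 14 to 17 points. This stands, so the figure should always be quoted with its base rate.
- **Back-fitting.** Declaring 9% v 20% because it matches 149 would fit an effect to a size, and nothing in the article supports 20% as expected or relevant. This also stands and affects the order of the remedies.

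**Conclusion.** The concern holds. The printed inputs need 42 to 53 patients per group (84 to 106 in total before loss), against the stated 149 (298). At 149 per group the power for 9% v 33% is about 99.9%, not 80%. At 80% power that size fits 9% v about 20–21%, or about 18–19% v 33%.

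The result assumes a two-sided 5% test, 1:1 allocation and one comparison of two independent proportions. One-sided testing lowers the requirement further. None of the alternative tests, base rates for a 24-point difference, or multiplicity splits tried reaches 149 at 80% power. The document does not settle whether a rate, the power or the calculation is wrong. The conclusion also does not depend on whether 9%, taken from complete injuries, suits this trial's population. It needs correcting because this is the only numerical justification of the trial's size, and it is false as written.

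**What to change.** First establish which pair of rates, power and alpha went into the calculation. Then rewrite the Sample size section so that its numbers agree, with the values substituted into the formula and the sidedness of the test stated.

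- **If a different pair of rates, or a different power, was used:** print it and say where it comes from.
- **If 9% v 33% is the smallest effect of interest:** give the requirement as about 42 to 53 per group, according to the formula chosen. If the larger enrolment is kept, give the reason.
- **If the planned size is kept whatever the origin of 149:** state that 149 evaluable patients per group give over 99% power for 9% v 33% and, at two-sided 5%, 80% power for 9% v about 20%. Present the second pair as what the size can detect, not as an expected effect, unless there is evidence for it.

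Carry any change through to the 298, the 328 and the abstract. The cost is one corrected paragraph. Keeping the planned enrolment requires no extra patients, visits or data.

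### The stated 149 patients per group does not follow from 33% versus 9% at 80% power and 5% error; those inputs give about 42 to 53 per group

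*Protocol article*

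**What the plan says.** The Sample size section of the protocol article gives every input to the calculation. For the control rate, the proportion gaining at least 5 motor points in a previous study at the same institution "evaluating the timing of decompression in a complete SCI was 9" per cent. The target for the other arm reads "early decompression group is 33% of patients demonstrating at least a 5-point improvement in summed motor score". The error rates follow: "To detect this difference with a sensitivity of 80% and an error probability of 5" per cent. From these the section concludes that "at least 149 patients per randomization group will be required".

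It then doubles that number, "Considering only comparing the two groups of early and late decompression, our sample size should be at least 298 cases", and inflates it: "To account for the possibility of 10% loss to follow-up, our estimated sample size is 328 cases". The Abstract carries the total forward as "328 selected spinal cord injury patients".

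The section on descriptive and explorative statistics confirms that the sample size and the main analysis both rest on this yes/no improvement variable.

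**The concern.** A difference of 24 percentage points from a low control rate is large, and a comparison of two proportions needs few patients to detect it with 80% power. A requirement of 149 per group looks about three times too high. If so, the inputs and the result printed in the same paragraph cannot both be right.

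What is at stake is the stated basis of the design. If the rates and the power are as printed, the trial plans to enrol about three times what they call for. If 149 is the intended number, the trial was sized for a smaller effect or under other error rates, and the article does not give them. The total of 328 in the Abstract rests on this step.

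**Working it through.** **Inputs (Sample size section).** p1 = 0.33, p2 = 0.09, difference d = 0.24, mean rate 0.21, power 80% (z = 0.8416), error 5%. Sidedness is not stated. I take two-sided (z = 1.960) and also show one-sided. Allocation is 1:1, inferred from the equal group sizes and the blocks of four under Randomization.

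**The plan's own chain.** 149 × 2 = 298, and 298 × 1.10 = 327.8, rounded to 328. These two steps reproduce. The step from the inputs to 149 does not.

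**Patients per group for 33% versus 9%, two-sided 5%, 80% power.**

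- Pooled variance: n = [1.960 × √(2 × 0.21 × 0.79) + 0.8416 × √(0.33 × 0.67 + 0.09 × 0.91)]² / 0.24² = [1.960 × 0.5760 + 0.8416 × 0.5505]² / 0.0576 = (1.129 + 0.463)² / 0.0576 = 44.02, so 45.
- Unpooled variance: n = (1.960 + 0.8416)² × (0.2211 + 0.0819) / 0.0576 = 7.849 × 0.3030 / 0.0576 = 41.3, so 42.
- Continuity-corrected: n = (44.02 / 4) × [1 + √(1 + 4 / (44.02 × 0.24))]² = 52.01, so 53.
- One-sided 5%: 35, or 43 with continuity correction.

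The stated 149 is 149 / 53 = 2.8 to 149 / 45 = 3.3 times the corrected and pooled results. In total, the stated inputs need 90 evaluable patients (106 with continuity correction), which is 100 (118) after dividing by 0.90.

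**Can another convention give 149?** None of those tried does.

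| Variant for 33% versus 9% (two-sided, 1:1, pooled unless noted) | Per group |
|---|---|
| 90% power | 59 |
| 95% power | 72 |
| 99% power | 101 |
| 1% error, 99% power, continuity-corrected | 141 |
| Largest possible variance (both rates treated as 50%) | 69 |
| Error divided by 6 | 69 (77 continuity-corrected) |
| Sizing complete and incomplete injuries separately (2 × 45) | 90 (106 continuity-corrected) |

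The arcsine method gives 42, and unequal allocation does not produce 149 either.

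**What 149 per group delivers.**

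- Power for 33% versus 9% (pooled formula): z = [0.24 × √149 − 1.960 × 0.5760] / 0.5505 = (2.930 − 1.129) / 0.5505 = 3.27, so power is 0.9995. With 134 per group (149 less 10%) it is 0.9986.
- Rate detectable at 80% power against 9%: solving n = 149 gives 20.5% with the pooled formula, a difference of about 11.5 points. With continuity correction it is about 21%.

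**Loss to follow-up.** 298 × 1.10 = 327.8 is the figure used. But 328 × 0.90 = 295.2, below the 298 the section sets as its minimum. Keeping 298 after 10% loss needs 298 / 0.90 = 331.1, so 332. The gap is 4 patients.

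**The case against.** **The formula is not visible.** The section refers to a formula that the text to hand does not show. That is no fault of the plan, and it means the source of the discrepancy cannot be traced. It does not rescue the number, because no standard two-proportion formula gives 149 from the stated inputs.

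**A larger trial has its uses.** The 9% comes from complete injuries only, while the trial enrols complete and incomplete injuries and compares each separately as a secondary purpose. That is a fair reason to want more patients. The Sample size section does not offer it, however. It ties 149 to the stated difference, and sizing the two strata separately gives 90 to 106 per arm.

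**Oversizing does not threaten validity.** This stands. For 33% versus 9% the primary comparison is not underpowered, and a reader should not infer that it is.

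**The loss inflation is trivial.** This also stands. Multiplying by 1.10 is a common shortcut, the gap is 4 patients in 332 (1.2%), and 147 per group instead of 149 still gives 79.7% power for 9% versus 20.5%. The data collection section also uses the latest available examination, so not every patient who misses the 12-month visit is lost to the analysis.

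Two stronger readings are tempting, and the document supports neither:

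- A reader might infer that every surplus patient is randomised to delayed surgery. Allocation is 1:1, so about half would go to early surgery. The Ethics section presents the late arm as ordinary care and says that operating after 24 hours raises no ethical concern.
- A reader might infer that a null result could not be interpreted. What the completed trial excludes will be read from its confidence intervals, and odds ratios with 95% intervals are planned. The error obscures why the trial has this size, not what its result will mean.

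**Conclusion.** The inconsistency is real and lies within one paragraph. The printed inputs call for about 42 to 53 patients per group, not 149, and 149 per group has about 99.9% power for the printed difference rather than 80%. A rate, the power or the sample size is misstated, and the document does not show which. The direction is towards oversizing for the stated effect, and the effect the trial is really sized for is not given.

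This rests on 1:1 allocation and a two-sided 5% test; a one-sided test widens the gap. The figure of 20.5% also assumes that the 9% control rate and the 80% power are correct and that the pooled formula applies. It describes what 149 per group can detect and is not evidence of what was intended. The error in the loss inflation is correct as a point of arithmetic but would not merit a comment by itself.

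**What to change.** Restate the Sample size section with the rates, power, error level, sidedness and formula actually used, so that inputs and sample size agree. The first step is to check the source calculation, because the misprint may be in a rate or in the power and not in the 149.

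If 328 is kept, state that 149 per group has about 99.9% power for 33% versus 9%, and 80% power for about 9% versus 20.5% (pooled formula; about 21% with continuity correction). If a smaller effect was the real target, name it and say why it matters clinically, rather than adopting 20.5% because it fits.

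In the same edit, state that 328 with 10% loss leaves about 295 evaluable patients; keeping 298 would need 332.

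The cost is the rewording of one paragraph. If 328 is kept, enrolment does not change.
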